### Participants

We will include n=180 patients with acute/subacute ‘sciatica’ and n=168 healthy age and gender-matched participants without symptoms of sciatica/LBP. Healthy participants are important to establish normative values for blood markers, somatosensory profiling and neuroimaging.

People aged >18 years with a clinical diagnosis of ‘sciatica’ will be recruited from primary care in Oxfordshire (eg, primary care providers for the National Health Service as wellGeneral Practitioners, Physiotherapy, Osteopathy and Chiropractor clinics) and through leaflets on public noticeboards. Sciatica symptom onset of the current episode needs to be within the past 3 months with a symptom-free period of at least 3 months preceding the current sciatica symptoms. The inclusion criteria for patients with ‘sciatica’ are based on a published diagnostic model,^19^ which includes five weighted parameters (self-reported sensory changes, below knee pain, leg pain worse than back pain, neurodynamic tests and neurological deficit). A sum score >4 will be defined as sciatica, with a mean predicted probability of 83%. In addition, patients with suspected sciatica will undergo a clinical examination by a physiotherapist to further confirm the diagnosis of sciatica and rule out other diagnoses (see the section additional phenotypic data below).

The following exclusion criteria will apply; presence of other nerve-related disorders (eg, diabetic neuropathy, stroke), previous lumbar spine surgery, serious spinal diseases (eg, infection, cauda equina syndrome, metastatic lesions), chronic inflammatory disorders, other pain conditions that may confound assessment (eg, fibromyalgia), pregnancy, insufficient command of the English language to obtain consent/complete questionnaires and contraindications to MRI for those selected for scanning.

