To investigate factors that predict pain persistence in people with sciatica, we will use variable selection techniques followed by predictive modelling. First, we will perform filtering of the original variables by calculating the univariate associations (coefficients, 95% CI, p values) between variables and the outcome and between each other. We will select a subset of uncorrelated variables that are associated with the outcome and use them as input features in machine learning algorithms for high-dimensional, small data sets that will allow us to identify the most powerful predictors and assess model selection/predictive accuracy. During preprocessing, missing data will be examined, the mechanism of missingness will be inferred using hypothesis testing and visually assessed using a matrix of boxplots for all pairs of variables and the outcome, and, if appropriate, multiple imputation by chained equations will be used. Drawing from machine learning techniques for high-dimensional small data sets, we will use resampling and validation in the form of repeated cross-validation to perform a complete variable profiling to identify the most powerful predictors. Multivariate adaptive regression splines (MARS) with built-in feature selection and Decision Tree models known to work well on low sample sizes will be trained to predict the 3-month and 1-year outcome. Model performance will be estimated using five times repeated 10-fold cross-validation and compared with models trained on surrogate data.^73^ The latter benchmarking technique is appropriate for small data sets, where holding out a subset of data before the analysis to be used as a pseudo-independent test set is impossible. Instead, an artificial—surrogate data set, preserving the descriptive statistics but not any of the potentially real associations between the variables and the outcome of the original dataset, will be created and the performance of models trained on the actual and surrogate dataset will be compared. Models’ predictive performance will be reported alongside variable importance rankings. Model selection will be done to maximise the Mathews correlation coefficient for dichotomised outcomes and to minimise the root mean square error for continuous outcomes during cross-validation. Scalar metric estimations of predictive performance including accuracy (binomial test p value against the majority class prevalence), balanced accuracy and the area under the precision/recall curve will be reported alongside their 95% CI. Predictor importance will be assessed using model specific techniques, that is, the reduction in performance estimated by cross-validation when each predictor is removed for MARS and node impurity for tree-based methods. Variables’ influence on the predicted outcome both at the global and individual level will be quantified by the partial dependence plots and individual conditional expectation,^74^ respectively. These will show the average marginal effect on the prediction given a certain value of a predictor variable and provide model interpretability.

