#### Predictor profiling

FORECAST aims to identify prognostic factors (the first step in the PROGRESS framework)^78^ rather than developing a clinical prognostic tool or individual risk model which requires much larger sample sizes. We will use robust algorithms that include feature selection, and we will assess model performance using methods developed for small data sets and robust metrics. As this part is an exploratory analysis that could shape future hypotheses and validation studies, our sample size is adequate. Given the anticipated sample size ratios with chronic (180×30%=54) and resolved sciatica (180×70%=126) and accounting for 15% attrition (see feasibility study), we will be able to identify moderate effects (effect size=0.5) using a two-tailed Wilcoxon-Mann-Whitney test (power 81%, alpha 0.05).

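### The plan infers the missingness mechanism from hypothesis tests and makes imputation conditional, but observed data cannot separate MAR from MNAR, and a non-significant test is weak evidence for MCAR

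*Protocol article*

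**What the plan says.** The handling of missing data is set out in one sentence of the Protocol article, in the prediction part of the Data analysis plan. Missing data are first examined. Then "the mechanism of missingness will be inferred using hypothesis testing", with boxplots of the variables and the outcome as a visual check. Finally, "if appropriate, multiple imputation by chained equations will be used". The sentence states no working assumption about the mechanism, and it names no handling other than MICE.

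The only allowance for lost data is in the sample size section, under Predictor profiling. It starts from "chronic (180×30%=54) and resolved sciatica (180×70%=126" patients, and "accounting for 15% attrition (see feasibility study") it claims to detect "moderate effects (effect size=0.5") with a "two-tailed Wilcoxon-Mann-Whitney test (power 81%, alpha 0.05"). The same section describes the predictor work as exploratory.

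**The concern.** The sentence commits to a method, so this is more than detail left to an analysis plan. An analysis plan that followed it would carry the problem forward.

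MAR and MNAR differ in whether missingness depends on the unseen values once the seen ones are accounted for. The observed data hold no information on that. A test of baseline variables by missingness status can reject MCAR and can do nothing more. The boxplots show the same observed values and have the same limit.

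The outcomes are self-reported bothersomeness and leg pain at 3 and 12 months, so dropout related to recovery is plausible. Two things are at stake. One is that a non-significant test is read as support for MCAR and imputation is left out. The other is that a significant test is read as establishing MAR, and dependence on the unseen 12-month outcome is then taken as excluded.

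**Working it through.** **1. The plan's own figure.** Inputs from Predictor profiling: 54 and 126 patients, 15% attrition, effect size 0.5, two-sided alpha 0.05.

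- After attrition: 54 × 0.85 = 45.9 and 126 × 0.85 = 107.1, together 153.
- Power ≈ Φ(d·√(n₁n₂/(n₁+n₂)) − 1.960). Here √(45.9 × 107.1 / 153) = √32.13 = 5.668, and 0.5 × 5.668 = 2.834, so power = Φ(0.874) = 80.9%.
- With the Wilcoxon efficiency 3/π it is 79.1%. The noncentral t gives 80.4% without that factor and 78.6% with it. A simulated Wilcoxon test with 46 and 107 patients gives 78.3%.

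The stated 81% is reproduced. No figure in the article is wrong on this point.

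**2. What one mechanism test can detect.** Lost: 180 × 0.15 = 27. Retained: 153. The article names no test, so a two-sided t-test of one baseline variable is assumed.

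- √(27 × 153 / 180) = √22.95 = 4.791.
- 0.5 SD: 0.5 × 4.791 = 2.395. The noncentral t with 178 degrees of freedom gives 66.4% power.
- 0.3 SD: 0.3 × 4.791 = 1.437, which gives 29.8% power.

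**3. What the test says about the mechanism.** Simulation with assumed values: n = 180, baseline–outcome correlation 0.3, outcome missing in about 13% to 16%, and log-odds of missingness rising by 0.5 or 1.0 per SD of the baseline variable (MAR) or of the outcome (MNAR). There were 4,000 runs per setting.

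| Mechanism | MCAR rejected | Bias in mean, complete cases (SD) | Bias in mean, MAR-based imputation (SD) | Complete-case slope (true 0.30) |
|---|---|---|---|---|
| MCAR | 5% | 0.00 | 0.00 | 0.300 |
| MAR, 0.5 | 57% | −0.02 | 0.00 | 0.299 |
| MAR, 1.0 | 99% | −0.04 | 0.00 | 0.299 |
| MNAR, 0.5 | 10% | −0.06 | −0.06 | 0.295 |
| MNAR, 1.0 | 24% | −0.14 | −0.13 | 0.274 |

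Outcome-dependent dropout passes the test in most runs, and a rejection does not say which of the other two mechanisms is at work. Imputation from the baseline variable alone removes the MAR bias in the mean but hardly touches the MNAR bias.

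**4. If complete cases were used.** The article gives neither missing rates per predictor nor the number of predictors that survive filtering. Assume p predictors, each missing independently at rate m, so that the remaining n = 153 × (1 − m)^p. Power is for effect size 0.5 by the noncentral t with the 3/π factor, so 78.6% is the value with no further loss.

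| p | m | Share kept | n left | Power |
|---|---|---|---|---|
| 10 | 0.5% | 0.951 | 146 | 76.5% |
| 20 | 2% | 0.668 | 102 | 61% |
| 50 | 2% | 0.364 | 56 | 38% |

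**The case against.** A reader might infer that a non-significant test sends the analysis to complete cases, and that so few patients would then remain that the models could not be fitted. The document does not support this.

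- It does not mention complete-case analysis, and no rule says that a test result cancels imputation. The words about appropriateness could refer to the amount or type of missing data.
- Only a filtered set of variables enters the prediction models, so deleting every patient with any gap across a hundred or so variables is not what is planned. Missing items also tend to cluster within a person, which reduces the loss, and decision trees can be fitted with incomplete predictors.
- The power figures above are for one test on one variable. With many variables tested, at least one rejection becomes likely, which would favour imputation.
- The study looks for prognostic factors, so associations matter more than outcome means, and the slope bias in the simulation was small.
- Default MICE alone barely reduces MNAR bias.
- A condensed article may leave imputation detail and sensitivity analyses to a separate plan.

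All of this stands, and it limits the size of the harm. It does not rescue the statement that testing will reveal the mechanism. That statement is in the text, and a more detailed plan that kept it would inherit the error.

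**Conclusion.** The point holds in a limited form. The stated procedure cannot deliver the inference it promises, and at about 27 lost against 153 retained, one non-significant test (66% power at 0.5 SD, 30% at 0.3 SD) is poor support for MCAR and should not settle whether to impute.

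How much harm follows is uncertain. The complete-case sizes, from 146 down to 56 of 153, rest on assumed missing rates, assumed numbers of predictors, independence across variables and a fallback that the article does not name. The bias figures rest on an assumed correlation and assumed dropout strengths. Under those, the MNAR bias in the mean is 0.06 to 0.14 SD for complete cases and the slope falls from 0.30 to between 0.295 and 0.274.

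This is a cheap improvement of modest severity, because the predictor analysis is declared exploratory and no stated figure is wrong.

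**What to change.** Change the missing-data sentence in the Data analysis plan as follows.

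- Keep the tests and boxplots, but describe them as checks for departure from MCAR. They neither establish the mechanism nor decide whether to impute.
- Make MICE under a MAR working assumption the default, fitted within the training folds of the repeated 10-fold cross-validation so that held-out data do not inform the imputation model.
- For the 12-month outcome, use as auxiliary variables the monthly pain diaries, the 3-month Sciatica Bothersomeness Index and pain rating, and the baseline values. The diaries and 3-month scores would inform the imputation only and would not become predictors.
- Add one delta-shift sensitivity analysis for the 12-month outcome, in which imputed values are moved by stated amounts in either direction. This is needed because MICE alone does not remove MNAR bias.

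The cost is plan wording and modest extra computing. All the auxiliary data are already being collected. The change should be made before the 12-month outcomes are analysed.

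### The predictor-importance ranking rests on repeated cross-validation, with no planned measure of how stable each variable's place in it is

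*Protocol article*

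**What the plan says.** For the second aim, the Data analysis plan describes a univariate filter, removal of correlated variables, and then MARS and decision-tree models. Repeated cross-validation is to be used to "perform a complete variable profiling to identify the most powerful predictors". The output is described as follows: the models' "predictive performance will be reported alongside variable importance rankings". Importance is defined as "the reduction in performance estimated by cross-validation when each predictor is removed for MARS", and as node impurity for trees.

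The section is specific about where uncertainty will be shown. Univariate associations come with 95% confidence intervals and p values. Accuracy, balanced accuracy and the area under the precision/recall curve come with 95% intervals. The surrogate-data benchmark compares the performance of whole models on real and artificial data; it is not applied to individual importances or ranks.

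The Predictor profiling section says that the aim is to find prognostic factors rather than to build a risk tool, and calls this part exploratory. Its only figure for this aim is a power calculation for a single comparison, a "two-tailed Wilcoxon-Mann-Whitney test (power 81%, alpha 0.05").

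**The concern.** Which variables are named, and in what order, is what later validation studies will take from this work. An importance rank is an estimate, and at about 153 patients it can move a good deal from one sample to the next.

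None of the planned safeguards shows that movement:

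- **Repeated 10-fold cross-validation** refits the models on largely the same patients, so a noise variable that happens to fit this sample tends to be picked again in most folds.
- **Univariate intervals** describe each variable's own association with the outcome, not its place in a multivariable ranking.
- **The surrogate comparison** can be passed because two or three variables are real, while noise variables sit beside them in the list.

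Readers would then be unable to tell stable entries from chance ones.

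**Working it through.** **1. The plan's own figure.** Inputs from Predictor profiling: "anticipated sample size ratios with chronic (180×30%=54) and resolved sciatica (180×70%=126"), "accounting for 15% attrition (see feasibility study"), and "moderate effects (effect size=0.5"). After attrition: 54 × 0.85 ≈ 46, 126 × 0.85 ≈ 107, total 153. Standard error of the standardised difference = √(1/46 + 1/107) = 0.176; 0.5/0.176 = 2.84; 2.84 − 1.96 = 0.88; power = Φ(0.88) ≈ 81%. The stated 81% is reproduced by the normal approximation. With the usual Wilcoxon efficiency of 3/π it is 78.6%. Either way it concerns one variable tested alone and says nothing about ranks.

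**2. Effect size as a correlation.** With p = 0.3, p(1−p) = 0.21 and d = 0.5: r = d√0.21 / √(1 + 0.21d²) = 0.229/1.026 = 0.223. If the two groups come from cutting a continuous outcome, the correlation with the uncut outcome is 0.223 × 0.458/0.348 = 0.294. The outcome section plans continuous outcomes, so 0.22 and 0.29 are both fair readings of the plan's effect size.

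**3. Overlap of training sets.** Within one repeat, two 10-fold training sets omit different tenths. They share 80% of all patients, which is 8/9 = 89% of each set. Two random half-samples share on average 25% of all patients, or half of each. In 216 simulated studies (153 patients, three true predictors at r = 0.30, 17 noise variables, simplified MARS), noise variables selected on the full data reappeared in 65% of cross-validation training sets but in 33% of half-samples. For true variables the figures were 98% and 78%.

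**4. Noise in the top five.** Assumptions: 153 patients, independent variables, continuous outcome, filter at p < 0.05, and 60 candidates. The article does not give the number of candidates. The 17 serum markers, about 18 sensory-test values and 20-25 questionnaire or body-chart scores make 55-60 before metabolomics. The top five is a device of this check; the plan sets no such list. The last column is the outcome variance explained by the true predictors, which for independent variables is the sum of r².

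| True predictors | Linear | Tree | MARS | Variance explained |
|---|---|---|---|---|
| 5 at r = 0.15 | 95% | 93% | not run | 11% |
| 5 at r = 0.22 | 79% | 88% | 81% | 25% |
| 5 at r = 0.29 | 24% | 68% | 28% | 43% |
| 5 at r = 0.40 | 0% | 25% | 0% | 80% |
| 10 at r = 0.15 | 78% | 80% | not run | 23% |
| 10 at r = 0.22 | 7% | 47% | 20% | 50% |
| 10 at r = 0.29 | 0% | 17% | 0% | 84% |
| 2 at 0.29, 3 at 0.20, 5 at 0.12 | 48% | 70% | not run | 36% |

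Entries are the share of simulated studies with at least one noise variable in the top five. With 100 candidates and five true predictors at r = 0.22 they are 90%, 96% and 89%. With 30 candidates the tree gives 61% in that setting.

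**5. Rank intervals.** With 60 candidates, a linear ranking and 200 bootstrap resamples in each of 120 studies, the median 95% rank interval of a top-five variable was about 1 to 38 (five true at 0.22), 1 to 36 (five at 0.29), 1 to 38 (ten at 0.22) and 1 to 39 (ten at 0.15). Variables that failed the filter in a resample were given the middle of the remaining ranks. An upper limit near 36-39 therefore means that the variable dropped out altogether in some resamples.

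**6. No true predictor.** 60 × 0.05 = 3 variables are expected to pass the filter by chance (2.99 in simulation). The ranking would still have entries.

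**Limits.** Real predictors are correlated, the MARS was simplified, and the tree was untuned (depth 4, at least 7 patients per leaf).

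**The case against.** The strongest reply is that a journal article condenses a fuller plan, so rank intervals may simply be left to it. If the point were only that something is unmentioned, this would succeed. It does not fully succeed here. The article fixes how importance is measured, says which quantities get intervals, confines the surrogate benchmark to whole-model performance, and names repeated cross-validation as the means of identifying predictors. That last choice cannot show the sampling error of the ranking.

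A second reply is that the work is exploratory, expects later validation, and also reports univariate intervals, partial dependence plots and individual conditional expectation. This stands as mitigation. A reader might infer that the plan shows no uncertainty about its predictors at all; it does, but not about rank or selection.

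A third reply concerns size. A reader might infer that the ranking will usually be contaminated by noise. The documents do not support that: they give neither the number of candidates nor the number and strength of true predictors, and the settings tried run from 0% to above 90%. With exactly five true predictors, any miss from a full top five also counts as noise entering. With ten equal predictors, some instability is true factors trading places. These points stand.

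Finally, a fixed selection cut-off has a price. In a check with 20 variables and 80 studies per setting, requiring 50% selection in half-samples kept 2.8 of 3 true factors at r = 0.30, but only 3.2 of 5 at r = 0.22 and 3.7 of 5 over r = 0.30 to 0.18. That is a loss of 36% and 26% in the last two. This also stands, and no such cut-off is recommended.

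**Conclusion.** The concern holds in a limited form. The plan names its strongest predictors from a ranking whose stability the stated methods cannot show, although it attaches intervals to neighbouring quantities. The size is conditional. At r about 0.22 with five true predictors among 60 candidates, a noise variable reaches the top five in about 80-90% of simulated studies. On the other reading of the plan's effect size (r about 0.29) this is 28% for MARS and 68% for trees, and for MARS it vanishes when effects are strong. The settings where it nearly vanishes for MARS have true predictors explaining 80% or more of the outcome variance. In all four settings where rank intervals were computed they covered more than half the list, subject to the ranking convention noted above. Since nobody can know beforehand which setting applies, the analysis should be able to reveal it. This should be changed, but it does not invalidate the study.

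**What to change.** Repeat the whole sequence (univariate filter, removal of redundant variables, MARS and tree fits) in bootstrap samples or random half-samples. Beside the importance ranking, report each variable's selection frequency and a 95% interval for its rank. Run the identical procedure on the surrogate data, so that importances and selection frequencies have a null reference. Describe low-frequency variables as unstable.

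No fixed threshold is needed. If the sponsor wants one, it should be set in advance and its loss of sensitivity stated. For example, with five true predictors at r = 0.22 among 60 candidates and a linear ranking, naming only variables in the top five of at least 60% of bootstrap samples left 0.09 noise variables on average, against about 1.2 in the bare top five. It kept 2.2 true ones, against at most 5 − 1.2 = 3.8.

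The cost is computing time, a few sentences in the analysis plan, and a more cautious list of named factors. No new data are required.

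### On its plain reading, one cross-validation both chooses the model and supplies its reported performance, so the reported figures are mildly optimistic; nesting the selection is a cheap improvement

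*Protocol article*

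**What the plan says.** All of this stands in the protocol article, Data analysis plan, unless another section is named.

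- **Candidates:** the families are "Multivariate adaptive regression splines (MARS) with built-in feature selection and Decision Tree models". For the time points, the text says that these "will be trained to predict the 3-month and 1-year outcome". Two families and two time points are named. The number of tuning settings is not.
- **Estimator of performance:** "Model performance will be estimated using five times repeated 10-fold cross-validation and compared with models trained on surrogate data".
- **Selection rule:** in the binary case, "Model selection will be done to maximise the Mathews correlation coefficient for dichotomised outcomes". In the other case, the stated goal is "to minimise the root mean square error for continuous outcomes during cross-validation".
- **Separate test data:** none, because with small data sets "holding out a subset of data before the analysis to be used as a pseudo-independent test set is impossible".
- **Reporting:** accuracy with a binomial p value against the majority class, balanced accuracy and the area under the precision/recall curve, with 95% CIs. The list is open-ended. MCC and RMSE are named only as selection criteria.
- **Outcome form:** the section on outcome measures makes the continuous outcomes the basis for analysis and keeps dichotomisation as an option for presentation.
- **Status:** Predictor profiling, under Sample size estimation, calls this part exploratory and says it is not meant to produce an individual risk model.

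**The concern.** Each cross-validated score is a noisy estimate. If several settings are scored on the same folds and the best is kept, its score combines real merit with favourable noise, so on average it exceeds the performance of that model in new patients. Repeating the 10-fold split five times averages over the splits. It does not remove the dependence on the one sample of patients, so it does not remove this effect.

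This is separate from any leak caused by filtering or imputing before the folds are made: it remains when the predictors are fixed and complete. At stake are the absolute performance figures, which later validation studies may use as a starting point.

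**Working it through.** **The plan's own figure.** The only number tied to this analysis is the 81% power in Predictor profiling. Inputs: 54 persistent and 126 resolved patients, 15% attrition, effect size 0.5, two-sided alpha 0.05.

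- Followed patients: 54 × 0.85 ≈ 46 and 126 × 0.85 ≈ 107, so N = 153.
- Power for two means: 0.5 / √(1/46 + 1/107) = 0.5 / 0.1763 = 2.836; Φ(2.836 − 1.960) = Φ(0.876) = 0.81.
- With the Wilcoxon efficiency 3/π: Φ(2.836 × √0.955 − 1.960) = Φ(0.811) = 0.79.

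The stated figure reproduces to within 2 points and is not at issue. The article states no expected MCC, accuracy or RMSE.

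**Simulation.** From the article: N = 153, 30% persistent, five times repeated 10-fold cross-validation, MARS and trees, selection by MCC or RMSE. Assumed, because the article does not give them: 10 predictors fixed in advance and complete (so no filter or imputation leak), 2, 8 or 39 candidate settings, and signal strengths R² = 0, 0.15 and 0.35. MARS was a simplified forward-hinge version. There were 120 data sets per signal strength.

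Optimism = cross-validated value of the selected model − its value in 4,000 new cases. For example, with 39 candidates and no signal, MCC optimism = 0.121 − 0.001 = 0.12.

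| Candidates | Measure | R² = 0 | R² = 0.15 | R² = 0.35 |
|---|---|---|---|---|
| 2 | MCC | +0.05 | +0.02 | +0.01 |
| 8 | MCC | +0.09 | +0.07 | +0.04 |
| 39 | MCC | +0.12 | +0.09 | +0.06 |
| 2 | Accuracy, points | +1.3 | +0.9 | +0.4 |
| 8 | Accuracy, points | +2.7 | +2.7 | +1.6 |
| 39 | Accuracy, points | +3.8 | +3.4 | +2.5 |
| 2 | RMSE | −0.1% | −0.1% | −0.1% |
| 8 | RMSE | −1.3% | −1.2% | −0.4% |
| 39 | RMSE | −2.3% | −2.5% | −1.3% |

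Monte Carlo standard errors of the means are about 0.01 for MCC, 0.004 for accuracy and 0.006 for RMSE. The two-candidate RMSE differences, and the two-candidate MCC difference at R² = 0.35, cannot be told from zero.

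**Is selection the cause?** One prespecified MARS, with no choice among candidates, gave cross-validated against true MCC of 0.02 v 0.00, 0.13 v 0.15 and 0.31 v 0.33. There is no material optimism without selection.

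**Effect on the binomial test.** The majority share is 107/153 = 0.699, with standard error √(0.699 × 0.301 / 153) = 0.037. The accuracy optimism therefore moves the test statistic by 0.004/0.037 ≈ 0.1 to 0.013/0.037 ≈ 0.4 standard errors with 2 candidates, and by 0.025/0.037 ≈ 0.7 to 0.038/0.037 ≈ 1.0 with 39. The centre of the 95% CI for accuracy moves by the same amount.

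**Surrogate comparison.** Two independent sets of 60 no-signal data sets, both put through the 39-candidate selection, differed in mean selected MCC by −0.005. The optimism cancels in the contrast when both sides are selected in the same way.

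**Nested cross-validation (39 candidates, one 10-fold outer loop).** MCC, nested / selected / true: 0.03 / 0.12 / 0.00 with no signal; 0.12 / 0.23 / 0.14 at R² = 0.15; 0.29 / 0.39 / 0.32 at R² = 0.35. Accuracy: 0.643 / 0.681 / 0.643; 0.668 / 0.705 / 0.671; 0.724 / 0.760 / 0.736.

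**A second, separately coded simulation** (22 settings, 80 data sets per case) agrees: selected 0.10 v true 0.00 with no signal, and 0.28 v 0.18 with three predictors at d = 0.5. Nested values were 0.00 and 0.15.

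**The case against.** The case on the other side has several good parts.

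- **The number of tries is unknown.** Two families are named and no grid is given. With two candidates the effect is small on every metric. This stands, and it is why the size is given as a range.
- **The larger figures belong to the optional outcome form.** Continuous outcomes are the main analysis, and for them RMSE is at most about 2.5% too low. This stands. The plan does, however, list classification metrics for reporting and sizes this part on a persistent/resolved split.
- **The performance of both families may be reported, not only the winner's.** The text allows that reading. It would remove the choice between families but not the tuning within each.
- **The article does not say that the loops are un-nested.** True; the full plan may nest them. But the article fixes the estimator, the selection rule and the absence of a hold-out, and describes one scheme only.
- **The analysis is exploratory and has safeguards.** A reader might infer that the study will present a model as predictive when nothing predicts. The documents do not support that. With no signal and 39 candidates, the average selected accuracy of 0.681 is still below the 0.699 majority share, so the binomial test gives some protection. The surrogate comparison gives more, if the surrogate data pass through the same selection; the article does not say whether they do. Neither safeguard corrects the absolute figures.
- **Nested figures err the other way when there is signal**, for example 0.15 against a true 0.18. This stands as a cost.

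**Conclusion.** The point holds in limited form. On the plain reading of the Data analysis plan, the reported metrics of the selected model, their 95% CIs and the binomial p value are optimistic, even with predictors fixed in advance. At N = 153 the optimism is about 0.01–0.12 in MCC and 0.4–3.8 points in accuracy, and RMSE is about 0.1–2.5% too low. Where in these ranges the study falls depends mainly on the number of candidate settings and on the true signal.

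The ranges rest on the assumed 10 predictors, candidate counts and signal strengths. A reader might also infer that MCC will be overstated by half. That ratio (0.28 against 0.18) belongs to one assumed grid of 22 settings and a weak signal. With two candidates at R² = 0.15 it is 0.160/0.137, about one sixth, and the article does not say which case applies. Given the exploratory aim and the continuous main outcomes, this is a worthwhile improvement and not a must-fix.

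**What to change.** In the Data analysis plan:

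1. List the candidate settings for MARS and for the trees.
2. Do the tuning and the choice between the two families in an inner loop (for example 5-fold) within each training set.
3. Take every reported metric, 95% CI and p value from the outer five times repeated 10-fold loop only.
4. Run the surrogate data through the identical nested procedure.

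The cost is a sentence or two of text and computing time: with a 5-fold inner loop, each setting needs 50 × 5 = 250 inner fits in place of 50, plus one refit of the chosen model per outer fold. The other cost is slightly conservative figures when there is real signal. No further patients or data are needed. If the full plan already nests the selection, one sentence saying so is enough. If it instead fixes one setting per family in advance and reports both, this source of optimism does not arise, and saying that would also suffice.
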